## Background

In vitro fertilisation (IVF) is the treatment of last resort for many subfertile couples and a very costly one, partly due to the use of expensive drugs, i.e. gonadotrophins, needed for controlled ovarian hyperstimulation (COH) [1]. COH is an essential part of IVF which is needed to obtain a reasonable yield of oocytes which can then be fertilised in vitro. In clinical practice physicians often rely on their clinical experience and judgement when selecting an appropriate starting dose of follicle stimulation hormone (FSH). There is neither international nor nationwide consensus about COH programmes. Defining the optimal dose of FSH to retrieve an acceptable number of oocytes remains complicated. The problem herewith is that women show marked differences in their ovarian reserve and, as a consequence, in their ovarian response to medication [2,3]. Women who respond poorly to ovarian stimulation have poorer pregnancy prospects than women with a normal ovarian response [4]. Frequently, the occurrence of an insufficient response will urge the clinician to cancel the cycle which is obviously very stressful to the couple and may lead to withdrawal from further treatment. In a subsequent stimulation cycle higher dosages of FSH are usually given, although these may also be inadequate, leading to another cancellation of the cycle or even to hyperresponse with risk of ovarian hyperstimulation syndrome (OHSS). The result is that the poor responder may go through a series of treatment cycles with an overall poor prospect for pregnancy.

On the other end of the spectrum, women with a hyperresponse to ovarian stimulation are at risk of increased patient discomfort, cycle cancellation and development of OHSS. This condition may lead to severe illness requiring hospitalisation and intensive care with thromboembolic phenomena or multiple organ failure which are potentially life threatening complications. Mild and moderate forms of OHSS occur in respectively 20–33% and 3–6% of all ovarian stimulation cycles, while the severe form of the syndrome has been reported to occur as frequently as 0.1–2% [5].

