### Study procedures

The AFC will be measured to assess ovarian reserve capacity. The AFC will be performed in the early follicular phase (cycle day 1–3) of the stimulation cycle by using a standard TVS based measurement and count of all ovarian follicles sized 2–10 mm in both ovaries, performed by experienced physicians trained in applying this ultrasound test. On the same day serum will be obtained for post hoc analysis of endocrine ovarian reserve tests. Based on the result of the AFC women will either receive a standard or elevated FSH dosage (RCT 1) or a standard or reduced FSH dosage (RCT 2). All predicted normal responders will receive the standard dose regime. Recombinant or urinary FSH will be used for ovarian stimulation. Stimulation with the assigned FSH dose will be initiated on cycle day 2 or 3. Dose adjustments in the course of the stimulation cycle are not allowed. A gonadotrophin-releasing hormone (GnRH) agonist (long or flare-up protocol) or antagonist co-treatment protocol will be used for luteinizing hormone (LH) peak suppression. The participating hospitals will apply only one of the methods of LH suppression for all participants included in the study (GnRH analogue stratification). Final oocyte maturation will be achieved by administration of human chorionic gonadotrophin (hCG) when three or more follicles of 17 mm are present. Oocyte retrieval will be carried out 34–36 hours after hCG administration. Embryo transfer will be performed 3–5 days after ovum pick- up. Luteal phase supplementation will consist of 600 mg micronized progesterone in three separate dosages starting one day after oocyte retrieval and continued until 18 days after ovum pick-up. All participants will undergo a maximum of three IVF or ICSI cycles during a treatment period of maximally 18 months.

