#### Experimental group

All women in the experimental group will receive an individualised FSH dose based on their AFC. If women in RCT 1 are randomised for dose adjustment they will use 450 IU FSH/day if the AFC is below 8 and 225 IU FSH/day if the AFC is 8-10. Women in RCT 2 will receive 100 IU FSH/day if they are randomised for dose adjustment. Participants will be subjected to the assigned dosage in the subsequent cycles. In RCT 1, dose adjustments are not allowed in a subsequent cycle. For women in RCT 2, dose adjustment in the second or third cycle is allowed, and can consist of a step of 25 IU FSH/day, if there is a poor response or hyperresponse (poor response is defined as the retrieval of less than five oocytes or the cancellation of a stimulation cycle because less than two follicles above 12 mm in diameter are observed on ultrasound; hyperresponse is defined as the retrieval of more than 15 oocytes or cancellation of a stimulation cycle because more than 20 follicles over 12 mm in diameter are growing and estradiol levels exceed 11.700 pmol/L (= 3187,08 ng/L) or if more than 30 follicles over 12 mm are growing).

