#### Control group

All women in the control group will receive a standard FSH dose of 150 IU/day, independent of the AFC classification. They will be subjected to the assigned dosage in the subsequent cycles. However, based on the response in preceding cycles, a dose adjustment in the second and third cycle is allowed, but cannot exceed a step of 50 IU FSH/day, if there has been a poor response or hyperresponse (as defined above).

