#### Outcome measures

The primary study outcome is the cumulative pregnancy rate achieved within 18 months after randomisation resulting in live birth. Pregnancies can be obtained in treatment cycles with fresh embryos as well as in subsequent cryo/thaw cycles. Spontaneous pregnancies between treatment cycles will also be taken into account.

The data will be integrated in a cost-effectiveness analysis. Differentiation will be made between direct medical costs (all health care sector costs), direct non-medical costs (costs outside the health care sector that are affected by health status or health care) and indirect costs of the fertility treatment (costs of sick leave due to fertility treatment). For medical costs, the process of care will be divided into two cost stages (cost of fertility treatment, cost of pregnancy), which can reoccur if women have repeat treatment cycles within the study period. These costs will be computed from the period of inclusion to the end of follow-up (18 months).

Direct non-medical and indirect costs may be generated if women are absent from paid work, either for visiting the fertility clinic during IVF or ICSI treatment or due to sick leave associated with physical or psychological side-effects of this treatment. The Health and Labour Questionnaire [13] will be used to document absence from paid work.

Fertility health care utilisation consists of hospital visits, TVS, gonadotrophins, endocrine laboratory tests, ovum pick-up, IVF or ICSI laboratory work and hospital care. Volumes of health care resource use will be measured alongside the clinical study in several participating centres by using a checklist.

Secondary study outcomes consist of the number of retrieved oocytes, the occurrence of poor response or hyperresponse, OHSS grade 2/3, the rate of cycle cancellation, the number of multiple pregnancies and total IU of FSH used per stimulation cycle.

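### A cycle cancelled with exactly two follicles above 12 mm cannot meet the hCG criterion, yet the definition does not count it as a poor response

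*Protocol article*

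**What the plan says.** Four places in the Methods of the protocol article bear on this.

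- **Definition (Experimental group).** Poor response has two limbs, one on retrieval and one on cancellation: "poor response is defined as the retrieval of less than five oocytes or the cancellation of a stimulation cycle because less than two follicles". The reason for cancellation reads in full "because less than two follicles above 12 mm in diameter are observed on ultrasound".
- **Trigger (Study procedures).** Final maturation is by "administration of human chorionic gonadotrophin (hCG) when three or more follicles of 17 mm are present". No other criterion for hCG is given. The dose may not be changed within a cycle.
- **Use as an outcome (Outcome measures).** The secondary outcomes include "the occurrence of poor response or hyperresponse, OHSS grade 2/3, the rate of cycle cancellation". Poor response and cancellation are thus reported separately.
- **Use as a dosing condition.** After a poor response or hyperresponse, in the RCT 2 individualised arm "dose adjustment in the second or third cycle is allowed, and can consist of a step of 25 IU FSH/day". In the control arms, on the same definition, "a dose adjustment in the second and third cycle is allowed, but cannot exceed a step of 50 IU FSH/day". The RCT 1 individualised arm has no such option.

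**The concern.** The cancellation limb stops at one follicle and the hCG criterion starts at three. A woman whose cycle is abandoned with two follicles has had an inadequate response and yields no oocytes, but read literally she has not had a poor response.

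Two things are at stake. First, the occurrence of poor response is meant to show whether dosing by antral follicle count improves ovarian response. As defined, moving a woman from one follicle to two, with both cycles cancelled, would register as a poor response avoided. Second, a control woman cancelled with two follicles would have to repeat 150 IU/day, because the condition for a step is not met. The Background section says that a higher dose usually follows an insufficient response, so this departs from the practice that the control arm is meant to represent.

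**Working it through.** No figure in the article needs reproducing here. The check sets the thresholds side by side for each number of follicles above 12 mm at the point where the cycle is stopped or triggered.

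**Inputs from the article:** retrieval limb, 0 to 4 oocytes; cancellation limb, 0 or 1 follicle above 12 mm; hCG, at least 3 follicles of 17 mm; 300 women per RCT.

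**Assumptions, not in the article:** at most one oocyte per follicle above 12 mm and none from smaller follicles; equal allocation within each RCT.

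| Follicles above 12 mm | hCG criterion can be met? | Label if cancelled for low response | Label if retrieved |
|---|---|---|---|
| 0–1 | No | Poor response | Not reachable under the criterion |
| 2 | No | **Not poor response** | Not reachable under the criterion |
| 3–4 | Yes, if at least three reach 17 mm | **Not poor response** | Poor response (at most 4 oocytes) |
| 5 or more | Yes, if at least three reach 17 mm | Not poor response | Depends on yield |

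**At two follicles.** Every 17 mm follicle is also above 12 mm, so three of 17 mm requires at least three above 12 mm. With two the criterion fails, and two is not fewer than two. The conflict therefore follows from the printed thresholds alone, without the yield assumption.

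**At three or four follicles.** The criterion can be met, and a retrieved cycle then counts as poor response under the yield assumption. The label changes only if the cycle is stopped for low response first.

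**At five or more.** The retrieved label is no longer fixed. With recovery probability p per follicle (assumed 0.7 to 0.8), the chance of fewer than five oocytes from five follicles is 1 − p^5:

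- p = 0.7: 1 − 0.168 = 0.832
- p = 0.8: 1 − 0.328 = 0.672

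From six follicles it is 1 − p^6 − 6p^5(1 − p):

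- p = 0.7: 1 − 0.118 − 0.303 = 0.580 (from unrounded terms)
- p = 0.8: 1 − 0.262 − 0.393 = 0.345 (from unrounded terms)

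**Scale.** 300/2 = 150 women per arm. One first cycle left uncounted lowers that arm's observed rate by 1/150 = 0.67 percentage points. This assumes a per-woman denominator; the article does not say whether poor response is counted per woman or per cycle. How many such cycles to expect cannot be derived, because no follicle distribution or cancellation frequency by count is given.

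**Arms with a step that depends on the definition:** RCT 1 control, RCT 2 control and RCT 2 individualised, so 3 of 4.

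**The case against.** The strongest reply is that the two cancellation clauses, for low and high response, are the trial's cancellation criteria restated inside a definition. On that reading a cycle with two to four follicles is not cancelled for low response. It goes to retrieval and is classed by oocyte count, so the limbs fit together. The hCG sentence says when to trigger, not what happens to a cycle that never gets there. The article also condenses a fuller protocol, where cancellation rules would normally be found.

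Part of this stands. At three or four follicles nothing in the article requires cancellation, and the problem needs a clinician to stop the cycle above the printed threshold. The Background remark that "the occurrence of an insufficient response will urge the clinician to cancel the cycle" describes usual practice, not a trial rule. A reader might infer that the definition mislabels every cycle with two to four follicles. The document supports that only at two; at three and four it is conditional.

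The reply does not work at two follicles. If fewer than two were the only ground for low-response cancellation, a two-follicle cycle could be neither cancelled for low response nor given hCG "when three or more follicles of 17 mm are present". That reading leaves this count without any stated path. Nor does the point rest on something the article leaves out: both numeric thresholds are printed, and they do not meet.

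It is also fair that two of the three arms with a dose step are in RCT 2, with antral follicle counts above 15, where so few growing follicles should be least common. The practical exposure is therefore mainly in RCT 1: the outcome in both arms, and the dose step in the control arm.

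**Conclusion.** The point holds and is minor. At exactly two follicles above 12 mm the definition and the hCG criterion conflict. At three or four, mislabelling arises only if a cycle is stopped for low response before the criterion is met.

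The consequences are confined to one secondary outcome and to an optional dose step in cycles 2 and 3. The step is permitted, not required, so what is lost is an option. The definition of the primary outcome, the sample size and the cancellation rate are untouched, and these cycles still appear in the cancellation rate.

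A reader might go further and infer that the comparison of poor-response rates is biased towards one arm. RCT 1 compares doses intended to change follicle growth, so the number of uncounted cycles could differ between arms. The article gives nothing from which to derive the size or the direction of such a difference, and none is claimed.

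**What to change.** Align the cancellation limb with the hCG rule: poor response means fewer than five oocytes retrieved, or a cycle cancelled for insufficient follicle growth because the hCG criterion was not met. At minimum, change the cancellation threshold from fewer than two to fewer than three follicles above 12 mm. The minimum change closes the conflict at two but leaves the conditional case at three and four.

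The cost is one clause. The definition already depends on the reason for cancellation and the follicle count, so no new kind of data is needed. The observed poor-response rate would rise slightly, and a few more women in the three arms above would become eligible for the optional step. The fuller wording would also count a cycle stopped with five or more follicles above 12 mm of which fewer than three reached 17 mm. Some of those might have yielded five oocytes if retrieved.

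Inclusion began in May 2011, so a changed dosing condition could apply only to later cycles. The outcome could be reclassified for all cycles if the reason for cancellation and the follicle count were recorded.

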#### Control group

All women in the control group will receive a standard FSH dose of 150 IU/day, independent of the AFC classification. They will be subjected to the assigned dosage in the subsequent cycles. However, based on the response in preceding cycles, a dose adjustment in the second and third cycle is allowed, but cannot exceed a step of 50 IU FSH/day, if there has been a poor response or hyperresponse (as defined above).

### Withdrawal of individual patients

Subjects can abandon the study at any time for any reason if they wish to do so without any consequences. The investigator can decide to withdraw a subject from the study for urgent medical reasons.

#### Outcome measures

The primary study outcome is the cumulative pregnancy rate achieved within 18 months after randomisation resulting in live birth. Pregnancies can be obtained in treatment cycles with fresh embryos as well as in subsequent cryo/thaw cycles. Spontaneous pregnancies between treatment cycles will also be taken into account.

The data will be integrated in a cost-effectiveness analysis. Differentiation will be made between direct medical costs (all health care sector costs), direct non-medical costs (costs outside the health care sector that are affected by health status or health care) and indirect costs of the fertility treatment (costs of sick leave due to fertility treatment). For medical costs, the process of care will be divided into two cost stages (cost of fertility treatment, cost of pregnancy), which can reoccur if women have repeat treatment cycles within the study period. These costs will be computed from the period of inclusion to the end of follow-up (18 months).

Direct non-medical and indirect costs may be generated if women are absent from paid work, either for visiting the fertility clinic during IVF or ICSI treatment or due to sick leave associated with physical or psychological side-effects of this treatment. The Health and Labour Questionnaire [13] will be used to document absence from paid work.

Fertility health care utilisation consists of hospital visits, TVS, gonadotrophins, endocrine laboratory tests, ovum pick-up, IVF or ICSI laboratory work and hospital care. Volumes of health care resource use will be measured alongside the clinical study in several participating centres by using a checklist.

Secondary study outcomes consist of the number of retrieved oocytes, the occurrence of poor response or hyperresponse, OHSS grade 2/3, the rate of cycle cancellation, the number of multiple pregnancies and total IU of FSH used per stimulation cycle.

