**Methods/Design:**

Multicentre RCT in subfertile women indicated for a first IVF or intracytoplasmic sperm injection cycle, who are aged < 44 years, have a regular menstrual cycle and no major abnormalities at transvaginal sonography. Women with polycystic ovary syndrome, endocrine or metabolic abnormalities and women undergoing IVF with oocyte donation, will not be included. Ovarian reserve will be assessed by measuring the antral follicle count. Women with a predicted poor response or hyperresponse will be randomised for a standard versus an individualised FSH regime (150 IU/day, 225-450 IU/day and 100 IU/day, respectively). Participants will undergo a maximum of three stimulation cycles during maximally 18 months. The primary study outcome is the cumulative ongoing pregnancy rate resulting in live birth achieved within 18 months after randomisation. Secondary outcomes are parameters for ovarian response, multiple pregnancies, number of cycles needed per live birth, total IU of FSH per stimulation cycle, and costs. All data will be analysed according to the intention-to-treat principle. Cost-effectiveness analysis will be performed to assess whether the health and associated economic benefits of individualised treatment of subfertile women outweigh the additional costs of an ORT.

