The key question in the economic evaluation is to assess whether the health and associated economic benefits of individualised treatment of subfertile women in terms of increased ongoing pregnancy rates and reduced rates of hyperstimulation, outweigh the additional costs of an ORT. The economic evaluation will be designed as a cost-effectiveness analysis with the costs per pregnancy resulting in live birth within 18 months as the primary outcome measure. Cost-effectiveness of each strategy will therefore be expressed as costs per live birth. The incremental cost-effectiveness ratio (ICER) of each individualised dose-adjustment strategy as compared to a strategy with standard FSH dose will be estimated as the ratio between difference in costs between strategies and the difference in pregnancy rates, and reflects the extra costs required to obtain one additional live birth. If in the predicted poor response group individualised FSH treatment following an ORT increases the live birth rate without affecting OHSS rates, individualised treatment is the dominant strategy. If in the predicted hyperresponse group individualised FSH treatment following an ORT reduces the rate of OHSS, without affecting live birth rates, individualised treatment is the dominant strategy.

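### Medical costs stop at 18 months while every birth from a pregnancy achieved by month 18 counts as effect, so the ICER omits later pregnancy and delivery costs of late conceptions

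*Protocol article*

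**What the plan says.** **Effect.** Under Outcome measures: "The primary study outcome is the cumulative pregnancy rate achieved within 18 months after randomisation resulting in live birth". The 18-month limit is attached to the pregnancy. The abstract (Methods/Design) is looser: "cumulative ongoing pregnancy rate resulting in live birth achieved within 18 months after randomisation".

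**When conception can occur.** Study procedures: "All participants will undergo a maximum of three IVF or ICSI cycles during a treatment period of maximally 18 months". Outcome measures adds: "Pregnancies can be obtained in treatment cycles with fresh embryos as well as in subsequent cryo/thaw cycles". Spontaneous pregnancies between cycles also count.

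**Costs.** For medical costs, Outcome measures says that "the process of care will be divided into two cost stages (cost of fertility treatment, cost of pregnancy", and then, of the costs in these stages: "These costs will be computed from the period of inclusion to the end of follow-up (18 months".

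**Ratio.** Economic analysis takes a societal perspective and uses "costs per pregnancy resulting in live birth within 18 months as the primary outcome measure". It defines the ICER as the cost difference divided by the difference in pregnancy rates, and reads it as the added cost per further live birth. No section extends costing beyond month 18 for pregnancies still ongoing then.

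**The concern.** The two halves of the main economic ratio run on different clocks. A pregnancy achieved at month 18 counts in full, although its birth falls near month 27. Its costs stop at month 18, so only the pregnancy care received by then is counted. Whether a credited birth is fully costed depends on when the woman conceived, not on what happened to her.

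This matters because cost-effectiveness is the trial's stated aim. The missing items, late antenatal care and delivery, belong to a cost stage that the article itself names. Multiple pregnancies are a secondary outcome, and the delivery costs of late ones are cut off in the same way. If the arms differ in the number of late conceptions, the missing cost does not cancel in the cost difference.

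**Working it through.** **The plan's own figures.** The article gives no conception times, gestation length or unit costs, so there is no stated economic figure to reproduce and no corrected ICER can be computed. The design rates used below come from its sample size section, which does reproduce. The check uses a two-sided alpha of 0.05, power of 80%, 1:1 allocation (assumed) and no continuity correction, with n per arm = [1.96·√(2p̄(1−p̄)) + 0.842·√(p0(1−p0)+p1(1−p1))]² / (p1−p0)².

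- RCT 1, 25% vs 40%: 152 per arm, 304 in total, against 300 stated.
- Both RCTs, 30% vs 41%: 296 per arm, 592 in total, against 600 stated.
- RCT 2, 35% vs 42% with 150 per arm: power 23.7%, against 24% stated.

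**Step 1: which conceptions are affected.** Assume 8.75 months (266 days) from conception to birth. Births fall after the cut-off when conception is later than 18 − 8.75 = 9.25 months. The latest credited birth falls at 18 + 8.75 = 26.75 months.

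**Step 2: late share s of credited births.** All timing patterns are assumptions. For conceptions uniform over 0 to H months, s = (H − 9.25)/H. For front-loaded conceptions, take an exponential with mean m before truncation at month 18, so s = (e^(−9.25/m) − e^(−18/m)) / (1 − e^(−18/m)).

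| Assumed timing | Calculation | s |
|---|---|---|
| Uniform, 0–18 months | 8.75/18 | 49% |
| Uniform, 0–12 months | 2.75/12 | 23% |
| Front-loaded, m = 9 | (0.358 − 0.135)/0.865 | 26% |
| Front-loaded, m = 6 | (0.214 − 0.050)/0.950 | 17% |
| Front-loaded, m = 4 | (0.099 − 0.011)/0.989 | 9% |
| All conceptions before month 9 | none late | 0% |

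**Step 3: number of births.** At the combined design rates with 300 per arm, births number 0.30 × 300 = 90 (standard) and 0.41 × 300 = 123 (individualised), a difference of 33. With the same s in both arms:

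- s = 9%: 8 vs 11 births without delivery cost, a gap of 3.
- s = 49%: 44 vs 60, a gap of 16.

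These pregnancies are incompletely costed, not uncosted: their care before month 18 is counted.

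**Step 4: effect on the ICER.** Let c be the mean omitted cost per late pregnancy, taken as equal in both arms, and let p and s carry subscript 1 for individualised and 0 for standard dosing. The cost left out of the difference is c(s1·p1 − s0·p0), so

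fully costed ICER = planned ICER + c(s1·p1 − s0·p0)/(p1 − p0).

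If s1 = s0 = s, the added term is s·c: between 0.09c and 0.49c per additional live birth under the late patterns above. It does not depend on the size of the treatment effect.

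**Step 5: the direction depends on timing.** Take the RCT 1 design rates, with conceptions earlier in the individualised arm (assumed s1 = 15%, s0 = 30%). Late births per 100 women are 40 × 0.15 = 6 and 25 × 0.30 = 7.5. The added term is c(0.060 − 0.075)/0.15 = −0.10c, so the omission would then count against individualisation.

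**Step 6: when it cancels.** If p1 = p0 and s1 = s0, then s1·p1 − s0·p0 = 0 and the cost difference is unaffected.

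**The case against.** **Birth by month 18.** Economic analysis refers to "costs per pregnancy resulting in live birth within 18 months". If that means birth by month 18, costs and effects share one horizon and there is no mismatch. A reader might infer that the error then reverses, because late treatment is charged without its birth. That does not follow: it would be ordinary truncation at a common horizon in both arms. But this reading is the less well supported one. Outcome measures ties the 18 months to the pregnancy, the ICER's denominator is the difference in pregnancy rates, and treatment itself may run to month 18. What stands is that the wording is ambiguous and needs settling.

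**Few conceptions may be late.** The antral follicle count is taken on day 1–3 of the stimulation cycle, allocation follows it, and FSH starts on cycle day 2 or 3, so the first cycle begins close to randomisation. With cycles starting near months 0, 6 and 12 and equal yield (assumption), only third-cycle conceptions, about one third, would deliver after month 18; cryo/thaw transfers would add some. A reader might infer that half of all births are affected. That needs conceptions spread evenly over the full 18 months, which the article does not support as a central case.

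**A condensed article.** Costing by stage, with resource volumes measured in several centres, is compatible with one unit cost per pregnancy, and the results will feed a decision model. Either could bring delivery costs back in. But the article states a cut-off for these very costs and describes no correction in the model. This is a conflict between stated rules, not a missing detail.

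**Conclusion.** The mismatch holds on the better-supported reading of the text. Followed as written, the cost rule leaves pregnancies conceived after about month 9 in the ICER as full live births with only part of their pregnancy cost and no delivery cost.

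The share of credited births affected cannot be fixed from the article. The 9–49% span rests on the assumed interval to birth and the assumed conception timing, and it would be zero if all conceptions came before about month 9.

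A reader might infer that the ICER is biased towards individualisation. The documents support that only conditionally: it requires more births in the individualised arm, as the design assumes, and similar conception timing in both arms. The protocol also hypothesises fewer cancellations and fewer poor-prospect cycles with individualised dosing. That could bring conceptions forward in that arm and shrink or reverse the effect. With equal birth rates and timing, as could apply in the hyperresponder scenario under Economic analysis where live birth rates are unchanged, the omission cancels.

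Without unit costs it cannot be shown that a cost-effectiveness conclusion would change. The clinical primary outcome and the sample size are not touched.

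**What to change.** Keep 18 months as the window for treatment and conception. Cost each counted pregnancy in both arms until it ends, including delivery and multiple births, either from recorded resource use or by applying unit costs to the known outcome. Under Outcome measures, limit the 18-month cut-off to fertility treatment and state that pregnancy costs run to the end of the pregnancy.

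Use one effect definition under Outcome measures and Economic analysis: live birth from a pregnancy achieved within 18 months of randomisation.

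The cost is a small amount of extra costing work for late conceptions. Live birth and multiple pregnancy must already be ascertained for these women. The change should be settled before the economic analysis starts, and any resource use that is to be measured directly must be collected while it is still available.
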